#### Hongi - Coming together

The next stage of the powhiri, the hongi (pressing of noses), the ha or breath of life is exchanged and intermingled. Through the exchange of this physical greeting, you are no longer considered manuhiri (visitor) but rather tangata whenua, one of the people of the land. The hongi is also a sign of life symbolising the action of Tane's breath of life to humans. By this action the life force is permanently established and the spiritual and physical bodies become a living entity.

This symbolises the end of the therapy, participants have had their mauri (life force) restored, rejuvenated and supported.

#### Hakari - Feast

Hakari is the act of ritual feasting that traditionally applied to the eating of cooked food. Symbolically, the hakari recognises the transition from the spiritual realm of the powhiri back into the physical world where food is shared.

At the completion of patient support and each of the PST sessions participants will be offered food and drink.

#### Poroporoaki - Farewell

Poroporoaki, or speeches of farewell, are reserved for the final part of the powhiri but are by no means the least important part of the process. The poroporoaki is the act of farewell and the return of mana (esteem and authority) to the host people. This is operationalised by the writing and sharing of a final discharge letter to other people involved in the participants care.

#### Intervention group

Māori randomised to the experimental group (Te Ira Tangata) who give their consent will be offered the following by the self harm team:

1. Patient support for up to two weeks. This will consist of one or two face-to-face or telephone sessions depending on patient preference and feasibility over the two week period following the participant's discharge from hospital. These sessions will involve obtaining the discharge plan developed by the assessing clinicians, checking that the patient understands it, identifying potential barriers to implementation of the plan and assisting the patient to follow through with the plan. In other words, the primary aim of patient support will be to ensure patients do not "fall through the cracks". The research clinicians will be expected to liaise with the mental health crisis and community mental health teams; alcohol and drug services; primary care and non health services. Each patient support session will include a risk assessment asking about thoughts and plans for self harm. If a patient is identified as being at risk of self harm the risk management protocol will be followed.

2. Postcard contact for one year. Eight postcards will be sent in sealed envelopes in months 1,2,3,4,6,8,10 and 12 after the index episode. The cards will contain a short message stating that we hope things are going well and inviting them to write us a note if they wish to (Additional file 2). Each envelope will contain a return stamped addressed envelope.

3. Problem solving therapy. This will consist of four to six sessions in the four weeks after the participant's index presentation to hospital for self harm. Research clinicians will assess the participant's eligibility for brief problem solving therapy prior to and at the initial patient support session. Patients may be ineligible for brief PST if they are already receiving psychotherapy (for example if they are receiving Dialectical Behaviour Therapy), if brief PST would contradict their management plan, if they live or are moving out of area, if they are in prison or if there is a risk of harm to the research clinician. The problem solving therapy we will use in the treatment package will be conducted with individual patients and is based on the model originally defined by D'Zurilla and Goldfried [21]. PST sessions will aim to teach the person to recognise and identify current problems and will provide them with a structured approach to problem solving. A clinician manual and a participant workbook will be used by the research team to guide the structure of PST sessions. Sessions will be audiotaped.

4. Improved access to primary care. We will encourage participants to attend their GP for a physical health check paying particular attention to cardiovascular risk factors especially alcohol and smoking. We will use GP vouchers to facilitate these visits.

5. A risk management strategy. The teams will also pilot a risk management strategy around the management of suicidal patients. This will consist of a checklist for patient support to ensure that key tasks are completed and questions asked. Secondly the research team will meet once a week to discuss adverse events defined as repeat episodes of self harm, hospital re presentation for any reason and suicides. A record will be kept of these discussions, including any changes to process as a result of these discussions, and circulated to the team in the form of a "risk bulletin". The research team will also receive training in crew resource management.

6. Cultural assessment. We have two aims here, the first is to increase the number of people who receive cultural services after self harm. From our previous study we found that the input of Maori services after self harm was very rare. The second aim will be to complete a cultural assessment on everyone paying particular attention to the sense of belonging and feelings around ethnicity. Problems with sense of belonging will be included in the problem solving checklist for patients.

#### Control group

Māori patients randomised to the control group who give their consent will receive treatment as usual and will be asked to complete a consent form and questionnaires at baseline, and questionnaires and telephone interviews at three months and one year. Treatment as usual following self harm varies and may involve referrals to multi-disciplinary teams for psychiatric or psychological intervention, referrals to crisis teams and/or recommendations for engagement with community alcohol and drug treatment centres. The discharge plan may include referrals to more than one health care provider, or may consist solely of referral back to the patient's General Practitioner.

##### Treatment as usual assessment

Treatment as usual for all participants will be assessed by self report using a written questionnaire and telephone interview by a research assistant blind to treatment allocation; a review of DHB records; and by using the National minimum dataset from the Ministry of Health Information Directory to record hospital contacts and contact with mental health services.

#### Outcome measures (Table 1)

**Table 1 T1:** Outcome measures

Outcome measure	Description	Explanation	Administered
**Primary**			

Hopelessness	Beck Hopelessness Scale (BHS)[22]	Scores below 9 on the BHS. Best predictor of subsequent self harm. Scores on a range of 0 to 20 with higher scores indicating greater hopelessness.	Entry, three and twelve months

**Secondary**			

Hospital repetition of self harm		Data on hospital contacts from participating DHB's and the New Zealand Health Information Service National Minimum Dataset	Three and twelve months

Depression and anxiety	Hospital Anxiety and Depression Scale (HADS)[23]	Self report scale. Scores of 10 and above on the anxiety and depression sub scales indicate clinically significant symptoms.	Baseline, three and twelve months.

Health status	EQ-5D [24]	A generic health-related quality of life index that can be related to costs.	Baseline, three and twelve months.

Self report repetition of self-harm		Self report assessed by telephone interviewer blind to allocation	Three and twelve months

Social functioning	SF-36 [25]	A generic measure of functional health and well being	Baseline, three and twelve months

Sense of belonging	Sense of belonging instrument (SOBI) [26]	Self report scale on sense of belonging to a community and ethnicity	Baseline, three and twelve months

Cultural identity	Cultural identity profile [27]	Produces four indicators of cultural identity, a secure, positive, notional or compromised identity	Baseline, three and twelve months

Seriousness of suicide attempt	Self rated objective part of the Beck Suicide Intent Scale (BSIS)[28]	Self report scale indicating the degree of suicidal intent of the self harm episode	Baseline

Costs following index attempt	Health service use, costs of attending care, cost of medication and time off work	Self report assessed by telephone interviewer blind to allocation	Three and twelve months

##### Intervention study

The primary outcome measure is the proportion of subjects who score below nine on the Beck Hopelessness Scale after one year (see sample size section for explanation).

Secondary outcomes are:

1. The proportion of subjects who repeat self harm by presenting to hospital at three months and one year after their index attempt.

2. Self reported repetition of self harm at three months and one year, assessed with a telephone questionnaire and a written questionnaire

3. Hopelessness measured by the Beck Hopelessness Scale at baseline, three months and one year

4. Anxiety and depression measured by the Hospital Anxiety and Depression Scale at baseline, three months and one year

5. Quality of life as measured by the EQ-5D (http://www.euroqol.org/) and the SF36 at baseline, three months and one year

6. Overall mortality (that is suicide deaths plus other causes of death) and suicide deaths at three months, one year, five years and ten years

7. Health service use at three months, one year, five years and ten years, assessed by a telephone questionnaire and interrogation of DHB and Ministry Of Health Information Directorate records

Outcome measures will be collected in several different ways.

##### Self report or self rating

Ratings scales will be by self rating. Self report will be to a researcher blind to the treatment allocation by a semi structured telephone interview which asks about repetition, health service use and economic measures (see attached copy of questionnaire).

##### DHB records

we will inspect these for episodes of repetition and health service use.

##### Ministry Of Health Information Directorate records

we will inspect these for health service use (both general and mental health), repetition and for mortality data. (It is necessary to look at national data on these measures as we found in our previous trial that at least 50% of people who self harm change address over twelve months often outside the DHB where they presented).

###### Self report by structured interview

Information for the economic analysis and self report of repetition will be gathered by telephone interview at three months and one year after the index attempt (Additional file 3). Telephone interviewers will be blind to the allocation of subjects. Blinding will be tested by asking the interviewers to nominate which group the subject was enrolled in. The economic analysis will also use a brief measure of quality of life the EQ-5D and interviewers will ask about health service use; costs associated with this; time off work; time off work for family to care for the participant; changes in benefit; changes in occupation; and drug use and cost. Participants will have the option of completing these measures in a face to face interview if, for example, they do not have a phone.

#### Process evaluation

A process evaluation will explore the implementation, receipt and context of the intervention with a view to helping understand the results in accordance with the Medical Research Council's guidelines [29] on assessing complex interventions. This will describe the processes in the intervention and control groups, provide information about the contexts in which the treatments are delivered and supply information about the experience of being part of the trial. The process evaluation is described in Table 2 below. The self-harm teams will also receive weekly supervision, the main themes of which we will incorporate into the process evaluation.

**Table 2 T2:** Process evaluation in Te Ira Tangata

Data collection method	Data collected
Programme documentation and observation (to assess fidelity, dose and reach)	Number of sessions of patient support Number of PST sessions Completion of PST Audiotaping of PST sessions Examination of written client PST research records Number of clients where sense of belonging addressed in PST Use of GP voucher Number of postcards sent Summary of discussions around adverse events Proportion of clients who received the interventions in each centre Proportion of clients not contactable after presentation to hospital
Structured interviews (to assess barriers, facilitators and suggestions for improvement)	Interview research clinicians re barriers and facilitators to the interventions plus suggestions for improvement Interview purposive sample of patients re what helped and what did not help plus suggestions for improvement Twelve month telephone interview of all patients what helped and what did not help Interview GP's who saw clients through GP voucher to assess their perception of the intervention and suggestions for improvement Interview focus group of staff in mental health and cultural services re barriers and facilitators to interventions plus suggestions for improvement

#### Process evaluation analysis

Numerical data will be entered into the Clinical Trials Research Unit web based data entry system specifically designed for this study. Information from the examination of patient notes and audiotapes will be used to assess the adherence of therapists to the manual in a 10% random sample of those who completed problem solving therapy. Data from structured interviews and focus groups will be analysed for emergent themes using NVIVO.

### Statistical methods

#### Power analysis

We know from the previous trial that approximately 310 Māori present with self harm each year to the general hospitals in Waitemata, Counties Manukau and Northland DHB's [30]. Of these 70% or 217 would have been eligible for this study. Assuming that we recruit participants at the same rate as the previous trial, that is 50% of eligible people, we would be able to recruit about 105 people a year from these DHB's, (or about 150 over eighteen months).

Traditionally the main outcome measure in self harm intervention research has been the proportion of people repeating after one year which is generally around 18% (29). However there are two problems here one of which is particularly relevant for indigenous people. Firstly to significantly reduce this by a third to 12% would need nearly 600 people in each arm of a trial (assuming a power of 80% with a significance level of 0.05). This is particularly problematic in trials involving indigenous people who are less numerous than the majority population. In New Zealand there are about 1000 episodes of self harm involving Māori each year which represents about 840 people. Assuming similar rates of eligibility and recruitment as in the earlier trial this means that the maximum number of Māori who could be enrolled in a treatment trial powered on a significant reduction in the repetition rate is about 300 people a year. In other words a trial would have to involve every DHB in the country and recruit people for four years. We suspect that the chances of funding any such trial are slim. The second problem with repetition rates is that although they are clearly a key consideration they are not important for the four out of five people who do not repeat. Other outcome measures such as measures of distress, quality of life and cultural identity are also significant. For these reasons we have decided that the main outcome we are interested in after one year is the proportion of people scoring below 9 on the Beck Hopelessness Scale. We have chosen this measure for several reasons, it is the best predictor of future self harm attempts; it is a significant marker of distress; and we know from previous research that individuals who score 9 or more on this measure are at least ten times more likely to kill themselves in the next year. Lastly in our previous trial we had outcome data at three months or one year on this scale in 85% of cases. In the previous ACC trial the proportion scoring 9 or more in both groups at baseline was 50%. Using this as the main outcome measure with 80% power, a significance level of 0.05 and a reduction in the proportion scoring above 9 from 50% to 25% after a year will require 66 people in each group, a total of 132. Allowing for 15% non completion of the Beck Hopelessness Scale we will need to recruit 155 people which should be feasible to collect over the fifteen months of recruitment into this trial. The figure of 155 participants is those people who have been randomised and consented to be in the study. We would expect that we would need to randomise about double this number of people to achieve this target.

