
### Analysis

#### Statistical analysis will be by the biostatistics team of the Auckland Clinical Trials Research Unit (CTRU)

Data from the trial will be entered into an Oracle database at the CTRU and extracted into SAS for analysis. All statistical analyses will be performed using SAS version 9.2 (SAS Institute Inc. Cary NC). All statistical tests will be two-tailed and a 5% significance level maintained throughout the analyses. Assessment of baseline comparability of the intervention and control group will be carried out via descriptive analyses for demographic information, method of self-harm, and previous history of self-harm. The proportion of people repeating self-harm in each group will be analysed using chi-squared test. We plan to analyse people whose index episode is a first presentation and those whose index is a repeat separately and together. The number of self-harm re-presentation episodes for the hospital and self report outcomes during follow-up will be analysed using negative binomial regression. Kaplan-Meier curves and Cox proportional hazards regression modeling will be used to analyze time to first re-presentation to hospital for self-harm and time to event for the mortality outcomes. The change from baseline to 3 months and one year in each of the repeated continuous outcomes will be analysed using mixed model regression. If baseline characteristics are found to be substantially different between the groups we will adjust for these in the regression modeling. All analyses will be conducted on patients who are randomised and consented except for the re-presentation to hospital and time to re-presentation outcomes which will be an intention to treat analysis that includes all randomised patients including those that did not consent.

In addition sensitivity analyses will be conducted using a CACE analysis [31] where appropriate which takes into account the fact that after randomisation not everyone in a Zelen design agrees to take part in the study. This has the effect of diluting any treatment effect and introducing a possible self selection bias. A CACE analysis is an attempt to correct for this. The assumption behind this is that those who consent to the intervention and treatment as usual are similar. We will test this by comparing the main factors which affect outcomes in both groups including the proportion of people presenting for the first time, gender and age.

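### The 80% power is not supported for the one-year comparison: the control rate is a baseline figure, and the loss allowance appears to count anyone with data at three months or one year

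*Protocol article*

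**What the plan says.** The Intervention study section fixes the endpoint: "The primary outcome measure is the proportion of subjects who score below nine on the Beck Hopelessness Scale after one year".

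The Power analysis section draws its planning figures from the sponsor's previous trial. The rate is introduced as "In the previous ACC trial the proportion scoring 9 or more in both groups at baseline was 50" per cent. The next sentence sets the design: "a reduction in the proportion scoring above 9 from 50% to 25% after a year will require 66 people in each group". The stated basis is 80% power at the 5% level. The section then allows 15% for non-completion of the Beck Hopelessness Scale (BHS) and arrives at 155 people randomised and consented.

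The only completion figure given is a little earlier in the same section: "Lastly in our previous trial we had outcome data at three months or one year on this scale in 85% of cases".

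The Analysis section settles sidedness: "All statistical tests will be two-tailed and a 5% significance level maintained throughout the analyses".

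**The concern.** A two-arm comparison at one year needs the proportion scoring 9 or more at one year under treatment as usual. The article supplies the proportion at entry, when patients have just presented after self harm, and uses it as if it were the one-year control rate. It does not argue that usual-care patients stay at 50% for a year. The Control group section describes usual care that may include psychiatric or psychological treatment, crisis teams, and alcohol and drug services, so some change over the year is plausible.

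The loss allowance has a similar problem. If 85% means data at either time point, then 15% is the fraction with neither. A participant with only a three-month score counts as complete in that figure but contributes no one-year primary outcome.

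The BHS endpoint was chosen partly because a trial powered on repetition was judged out of reach, so the case for feasibility rests on this calculation. If the real one-year inputs give materially lower power, a null result would be hard to interpret, and nothing in the article would warn the reader.

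**Working it through.** **Inputs from the article.** Two-sided 5% level; 80% power; 50% v 25%; equal groups; 66 per group; 15% loss; 155 recruited. All come from the Power analysis section except two-sidedness, which comes from the Analysis section.

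**Step 1. Reproduce 66 per group.** With p̄ = (p₁ + p₂)/2 and d = p₁ − p₂:

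n = [1.96·√(2p̄(1−p̄)) + 0.8416·√(p₁(1−p₁) + p₂(1−p₂))]² / d²

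For 0.50 v 0.25, p̄ = 0.375, and the two roots are 0.6847 and 0.6614. So n = (1.3419 + 0.5567)² / 0.0625 = 57.7.

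Continuity correction: n_c = (n/4)·[1 + √(1 + 4/(n·d))]² = 14.42 × (1 + 1.1302)² = 65.4, which rounds up to 66. The plan's figure is reproduced.

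**Step 2. Reproduce 155.** 2 × 66 = 132, and 132/0.85 = 155.3. Also reproduced, to within rounding.

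**Step 3. Compare each input's time point with the endpoint's.**

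| Input | What the test needs | What the article supplies |
|---|---|---|
| Control rate | Usual care at one year | Both groups at baseline |
| Completion | BHS at one year | BHS at three months or one year |

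**Step 4. Power with 66 per arm at other one-year rates.** The article gives no one-year rate, so the rates below the first row are assumptions.

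Power = Φ{[d√n − 1.96·√(2p̄(1−p̄))] / √(p₁(1−p₁) + p₂(1−p₂))}

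For the continuity-corrected figure, n is replaced by n·[1 − 1/(n·d)]². At d = 0.25 this turns 66 into 58.2.

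Example, 40% v 20%: (0.2 × 8.124 − 1.96 × 0.6481)/0.6325 = 0.561, and Φ(0.561) = 71%.

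| Control v package at one year | What is held fixed | Uncorrected | Corrected | Corrected n per arm for 80% |
|---|---|---|---|---|
| 50% v 25% | plan | 85% | 80% | 66 |
| 40% v 20% | halving | 71% | 64% | 91 |
| 35% v 17.5% | halving | 63% | 55% | 110 |
| 30% v 15% | halving | 54% | 46% | 134 |
| 40% v 25% | package arm at 25% | 45% | 38% | 165 |
| 40% v 15% | 25-point gap | 90% | 87% | 57 |

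The direction depends on what is held fixed. A lower control rate costs power if the package halves the rate or if the package arm stays at 25%. It adds power if the 25-point gap survives.

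**Step 5. Completion below 85%, with 155 recruited and 50% v 25%.** The completion rates below 85% are assumptions.

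| One-year completion | Per arm (155 × completion / 2) | Uncorrected | Corrected |
|---|---|---|---|
| 85% | 65.9 | 85% | 80% |
| 80% | 62.0 | 83% | 77.5% |
| 75% | 58.1 | 80% | 74% |
| 70% | 54.3 | 77.5% | 71% |

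**Step 6. Both together.** At 40% v 20% with 75% completion (58.1 per arm), power is 66% (58% corrected).

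**The case against.** The strongest reply is that this is a planning assumption, not an error of calculation. That is correct: both 66 and 155 reproduce, and a reader who inferred a faulty formula would be wrong.

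A reader might also infer that the trial is underpowered. The article does not support that. The previous trial's one-year results are not shown, so the usual-care rate could be near 50% or well below it. The article also does not say whether it is designing for a halving or for a 25-point difference. At 40% v 15% power would rise. That case needs a 62.5% relative reduction (25/40), for which the article offers no argument, but the article does not rule it out.

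A third tempting reading is that 50% to 25% is merely a before-after fall. The wording is loose, but 66 in each group comes from a two-group formula, so the figures do work as a between-arm contrast. The fault is where the 50% came from.

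On completion, the article never says that 15% is 100% minus 85%, although no other source is offered. The phrase about three months or one year could mean completion at each follow-up. Even on the either-point reading, the bound applies to the previous trial and not to this one, which gives a gift for completed scales and allows face-to-face interviews for the interview measures. The continuity correction also leaves slack: 75% completion still gives 80% power uncorrected. Against this, the Ministry of Health records section says at least half of people who self harm change address within twelve months, and the Discussion itself names completion of rating scales at follow-up as a potential issue.

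What survives is that neither figure is shown to apply at one year, and that the control rate is certainly a baseline figure.

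**Conclusion.** The point holds in limited form. The stated 80% power for 155 recruits is not supported for the one-year comparison, because the control rate is a baseline proportion used without justification and the loss allowance is, on its most natural reading, a lower bound on one-year loss in the earlier trial.

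The control rate is the main issue. Across the assumed one-year scenarios, uncorrected power with 66 per arm runs from 45% to about 90%, which shows how much turns on a figure the article does not give. The completion point is secondary: at the plan's own rates, ten points of extra loss take corrected power from 80% to 74%.

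This should be fixed, but it does not invalidate the design. Confidence is high that the time points do not match and moderate that the mismatch matters, since the shortfall, if there is one, cannot be sized from the article.

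**What to change.** 1. Replace the 50% with the previous trial's one-year proportion scoring 9 or more under usual care, or give the argument for no change from baseline.
2. Replace the 85% with that trial's completion of the BHS at one year alone, and state that the loss allowance is derived from it.
3. State whether the design target is a halving or a 25-point difference.
4. Restate the power, or the detectable difference, for 155 recruits. Add a short table over control rates of 30% to 50% and completion of 65% to 85%, showing both the constant-ratio and the constant-difference cases.

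Modelling the three-month and one-year BHS status jointly would let participants with only a three-month score contribute. That is an optional analysis choice and does not repair the planning inputs.

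The cost is a lookup in the sponsor's own earlier data and one rewritten paragraph. Restating the power needs no extra patients, but the stated figure may become less favourable.

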###### Termination of the study

Termination will be considered if there is 10% absolute greater number of adverse events (re-presentations to hospital for self harm) in the treatment group than in the usual care group at three months. Unblinded analyses to assess excess harm will be conducted at one year by an independent statistician at CTRU (not the study statistician). One year was chosen as any shorter time will mean that there will be few outcomes and any longer time is close to the end of the intervention at 18 months. For this analysis the Haybittle-Peto stopping boundary will be used which is based on a three standard deviation rule corresponding to a two sided test P = 0.003 stopping rule. This does not affect the power calculation of the study.

Ethical approval has been received from the New Zealand, Central Health Ethics Committee.

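### At the protocol's own accrual rate, fifteen months of recruitment gives about 131 to 136 participants, not the 155 called feasible

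*Protocol article*

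**What the plan says.** All the accrual figures are in the Power analysis section of the protocol article.

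- Source population: "approximately 310 Māori present with self harm each year to the general hospitals" in the three District Health Boards.
- Eligibility: "Of these 70% or 217 would have been eligible for this study".
- Uptake: "Assuming that we recruit participants at the same rate as the previous trial, that is 50% of eligible people".
- Projection: "we would be able to recruit about 105 people a year from these DHB's, (or about 150 over eighteen months".

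The section then derives the sample size: 66 per group for a fall from 50% to 25% with 80% power at the 0.05 level, 132 in total, raised to 155 for 15% non-completion of the Beck Hopelessness Scale. It concludes that "we will need to recruit 155 people which should be feasible to collect over the fifteen months of recruitment into this trial".

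It defines the 155 as people who are both randomised and consenting, and adds: "We would expect that we would need to randomise about double this number of people to achieve this target". The 155 is therefore counted in the same unit as the projected recruits, with the same uptake of about one half.

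A further reference to eighteen months stands under Termination of the study, where the timing of the one-year unblinded analysis is explained: "any longer time is close to the end of the intervention at 18 months".

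**The concern.** Within one section, a larger number is called feasible in a shorter time than the protocol has just projected: 155 in fifteen months, after about 150 in eighteen. The article gives no higher rate, additional site or extension to connect the two. The difference is not one of definition either, since both figures count consenting participants.

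The recruitment period drives staffing, funding and the planned end of enrolment. Feasibility also carries weight in this design, because the section rejects repetition of self-harm as the primary outcome partly on the ground that enough Māori participants could not be recruited. If the fifteen-month figure were taken as the real limit, the trial would have fewer evaluable participants than its own calculation calls for, with no margin for slower consent or greater loss to follow-up.

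**Working it through.** **1. Reproduce the sample size.** The inputs are p1 = 0.50, p2 = 0.25, d = 0.25, 80% power and 0.05 (Power analysis), with two-sided tests (Analysis).

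- Uncorrected: n′ = [1.960 × √(2 × 0.375 × 0.625) + 0.842 × √(0.25 + 0.1875)]² / 0.25² = 57.7, so 58 per group.
- With continuity correction: n = (n′/4) × [1 + √(1 + 4/(n′d))]² = 65.4, so 66 per group. This is the printed figure.
- Non-completion: 132 / 0.85 = 155.3, printed as 155.

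The sample size is sound, and 66 per group rests on the continuity-corrected formula.

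**2. Reproduce the accrual rate.** 310 × 0.70 = 217 eligible a year, and 217 × 0.50 = 108.5 recruited a year. The protocol rounds this to about 105. Both rates are carried forward.

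**3. Yield and time to target.**

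| Rate per year | 15 months | Short of 155 | 18 months | Months to 155 |
|---|---|---|---|---|
| 105 | 131.25 | 24 | 157.5 | 17.7 |
| 108.5 | 135.6 | 19 | 162.75 | 17.1 |

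The printed projection of about 150 in eighteen months is lower than 105 × 1.5 = 157.5. Taken literally it means 100 a year, which gives 125 in fifteen months and needs 18.6 months to reach 155.

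**4. Rate needed for fifteen months.** 155 / 1.25 = 124 a year, and 124 / 217 = 57% of eligible people consenting, against the stated 50%.

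**5. Consequence for power if recruitment did end at fifteen months.** Evaluable: 131.25 × 0.85 = 111.6 and 135.6 × 0.85 = 115.3, so about 112 to 115 against 132, or 55.8 to 57.6 per group.

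Uncorrected power is Φ{[d√n − 1.960 × √(2 × 0.375 × 0.625)] / √(0.25 + 0.1875)}. For corrected power, n is first replaced by n′ = (n − 1/d)²/n, which inverts the correction in step 1.

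| Recruited | Evaluable per group | Corrected power | Uncorrected power |
|---|---|---|---|
| 131.25 | 55.8 | 72.3% | 78.6% |
| 135.6 | 57.6 | 73.9% | 80.0% |
| Plan's target | 66 | 80.4% | 85.1% |

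**6. Is the number to be randomised a second failure?** Doubling 155 gives 310 to randomise, while 217 × 1.25 = 271 eligible people would present in fifteen months. The ratio 271/310 is 0.875, and 135.6/155 is also 0.875. It is the same shortfall divided by the same 50% uptake.

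**The case against.** The strongest reply is that fifteen months is a forecast and not a closing rule. The article does not say that enrolment stops at fifteen months whatever number has been reached, and it says equally plainly that 155 people are needed. A reader might infer that the trial will close 19 to 24 people short, but the text does not support that. This part of the reply stands, so the power figures above are conditional.

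The rate is also approximate, so 155 in fifteen months is not impossible. It is unsupported, however. It needs 57% uptake, and the section itself repeats an uptake of about one half. If arrivals are taken as Poisson at the stated rate (an assumption), the chance of 155 or more in fifteen months is about 2% at a mean of 131.25 and 5% at 135.6.

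A reader might also conclude flatly that 80% power would be lost. That holds only on the continuity-corrected basis. The article names no test for the primary outcome. The one test it names for a proportion, a chi-squared test for repetition, comes with no mention of a correction. Uncorrected, power at fifteen months is 79–80%, because the correction left some slack in 66 per group. Both figures must therefore be given.

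Finally, the eighteen months under Termination of the study might be read as confirming the recruitment period. That sentence speaks of the end of the intervention and does not settle when recruitment ends.

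None of this removes the contradiction. Nor is it a matter of an article condensing a fuller document, since both figures are printed in the same section and they conflict.

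**Conclusion.** The recruitment period and the feasibility statement are wrong on the protocol's own figures; the sample size is right. At 105 to 108.5 consenting participants a year, fifteen months gives about 131 to 136 people, which is 85–88% of 155, and the target takes 17.1 to 17.7 months. The printed eighteen-month figure of about 150 also misses 155 and understates what the stated annual rate yields.

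The effect on power arises only if recruitment ends at fifteen months, accrual follows the stated rate and 85% complete the scale. Corrected power is then 72–74% against 80%, and uncorrected power 79–80% against 85%. The documents do not show whether the period or the rate is the mistaken figure.

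Severity is moderate. The target sample size, endpoint and analysis are untouched, but a figure used to plan enrolment cannot stand as printed.

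**What to change.** Make the accrual projection and the feasibility statement in the Power analysis section agree, in one of three ways:

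1. State a recruitment period of about eighteen months and correct the projection of about 150 to about 158 (105 × 1.5). Changing fifteen to eighteen alone would leave 150 against 155.
2. If fifteen months is fixed, state the expected numbers as about 131 to 136 recruited and 112 to 115 evaluable, with power of about 72–74% (continuity-corrected) and 79–80% (uncorrected).
3. Keep both fifteen months and 155, and justify a rate of about 124 a year, that is, 57% of eligible people consenting.

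Under Termination of the study, only clarify what the eighteen months refers to.

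The change of text is a sentence or two. The first option costs about three more months of recruitment, a length that the accrual projection already uses. The second costs a less favourable stated power. The third needs evidence for higher uptake, which the article does not now contain.
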